## Abstract

**Background:** Cerebrovascular diseases are the leading cause of cognitive decline and dementia. Therefore, the investigation of the potential ways to slow down the disease progression is an important research field. Periodic limb movements in sleep (PLMS) are known to be associated with transient changes in heart rate and blood pressure. These changes might influence the course of cerebral small vessel disease (cSVD). Nevertheless, the clinical significance of PLMS, particularly its influence on cardiovascular diseases course, is still controversial and underinvestigated.

**Methods/design:** Patients from 60 to 75 years old diagnosed with cSVD will undergo nocturnal polysomnography. Subjects with apnea/hypopnea index under 5 will be enrolled. Sleep quality and daytime functioning will be assessed at baseline with self-reported questionnaires. Brain MRI and cognitive assessment will be performed at baseline and in the 2-year follow-up. Progression of cSVD markers and cognitive dysfunction will be compared between patients with PLMS index (PLMI) equal to or more than 15 movements per hour of sleep and controls (PLMI <15/h).

**Discussion:** The negative role of PLMS in cSVD progression and related cognitive decline is expected. We suppose that patients with PLMS tend to worsen in cognitive performance more rapidly than age-, gender-, and comorbidity-matched controls. We also expect them to have more rapid white matter hyperintensities and other cSVD marker progression. The limitations of the study protocol are the short follow-up period, the absence of a treatment group, and inability to make a conclusion about causality.

## Introduction

### Background

Cerebrovascular diseases (CVD) remain a global problem today because of high prevalence and related cognitive impairment. Increase in vascular dementia rate is the current trend worldwide. Thus, the identification of new predictors for CVD seems to be an important medical and social problem. Cerebral small vessel disease (cSVD) is one of the most prevalent forms of CVD. This term is used to describe clinical features and structural changes in brain tissue occurring due to damage of small perforating arterioles as well as capillaries and venules. This vascular pathology results in white tissue and basal ganglia lesion that leads to neurological deficit and cognitive decline (1). cSVD is considered to be the leading cause of cognitive dysfunction and dementia (2–4). Moreover, cSVD is associated with an increasing risk of cerebral infarct and intracranial hemorrhage (5, 6). However, cSVD is a broad term, and it encompasses “pure cSVD,” Binswanger's disease, and mixed dementia (when Alzheimer's disease overlaps with cSVD), which are inherited forms of cSVD (7).

Although there are generally accepted risk factors for cSVD including hypertension, diabetes, and aging (1), recent researches have demonstrated a significant role of sleep disturbances in cSVD progression. The significance of obstructive sleep apnea is now well-established and extensively reported (8, 9). Nevertheless, there is a growing body of literature that recognizes the negative influence of other sleep disorders, including periodic limb movements (LMs) in sleep (PLMS), on the course of cardiovascular diseases and cSVD in particular. A probable explanation of this impact is a sleep fragmentation that results in episodes of heart rate increase and blood pressure elevation (8–12).

PLMS is a condition characterized by periodic episodes of repetitive and stereotypic flexions of the hips, knees, and ankles (less common—arms movements) that manifests during the sleep. Diagnosis of periodic limb movements disorder (PLMD) requires conformity with two criteria. Firstly, periodic limb movements index (PLMI) >5/h in children and >15/h in adults must be detected by polysomnography (PSG). Second, PLMS in sleep must lead to clinically significant sleep disturbance or impairment in different relevant areas of functioning and cannot be better explained by another current sleep, medical, or neurological disorder such as narcolepsy, restless leg syndrome (RLS), or REM sleep behavior disorder (13, 14). The prevalence of PLMS worldwide, including the Russian population, is estimated to be 3.9–6% in the general population and around 34% in aged patients (above 60 years) (15, 16).

PLMS are described to be associated with various conditions, such as congestive heart failure (17), alcohol abuse (18), Tourette syndrome (19), syringomyelia (20), multisystem atrophy, and Parkinson's disease (21). Increased PLMS are also observed in a significant proportion of patients with various sleep disturbances (narcolepsy and obstructive sleep apnea). Moreover, this phenomenon is also detected in healthy subjects, and the prevalence increases with age (13, 16, 22). The closest association of PLMS is found with RLS. Approximately 85% of patients with RLS show high PLMI during nocturnal sleep (13, 22).

### Pathophysiology and Cardiovascular Effects of PLMS

Initially, PLMS were studied in close connection with RLS. These conditions are supposed to share common pathophysiological mechanisms since E. Lugaresi et al. showed that most RLS patients had periodic leg movements during sleep (23, 24). RLS is defined by the International Classification of Sleep Disorders (III Edition) as the syndrome characterized by an urge to move the legs, sometimes accompanied by an uncomfortable sensation that occurs primarily with rest/inactivity; it is partially or totally relieved by movement, for as long as the movement occurs, and occurs primarily in the evening or at night (14). Despite close relations between PLMS and RLS, they are considered to be different neurological processes since one of them can occur in the absence of the other (23), although the precise origin of PLMD and RLS is not established. Probably, dopamine or its derivatives play the primary role in these states because a high prevalence of both RLS and PLMS is observed in Parkinson's disease patients (25). Moreover, worsening of symptoms is observed after dopamine antagonist intake and vice versa; remarkable improvement can be achieved by dopaminergic agent intake (26). On the other hand, Manconi et al. investigated the role of dopamine using pharmacological agents and revealed that RLS can be reduced using both dopaminergic and non-dopaminergic agents, whereas PLMS respond to dopaminergic agents only (27). Thereby it is likely, that PLMS is under stronger dopaminergic control in comparison with RLS.

The dysfunction of descending inhibitory pathways with subsequent disinhibition of the segmental apparatus of the spinal cord is believed to be the reason for PLMS (28). The D2 and D3 receptors on the preganglionic neurons of the lateral horns are considered to be involved (29). Probably, the diencephalic dopaminergic structures (A11 neuronal group) take part in the genesis of PLMS and RLS because the A11 diencephalospinal pathway is crucial for pain control and sensorimotor integration at the spinal level (30). For example, the study on rats showed the presence of A11 dopaminergic terminals in posterior spinal horns and their vicinity to the motor neurons of anterior horns (31). The model involving the crucial role of dopamine could explain the positive effect of intake of dopaminergic agents in patients with both PLMS and RLS.

The subcortical origin of PLMS is confirmed by the experiment with paired-pulse transcranial magnetic stimulation (ppTMS). Rijsman et al. revealed decreased intracortical inhibition and increased intracortical facilitation while the cortical excitability was normal in subjects with RLS and PLMS. These aberrations appeared more significant in the leg that was more disturbed with sensorimotor symptoms and had higher PLMI than the other leg (28). The presumption about the supraspinal subcortical origin of PLMS is confirmed by studies in patients with cervical or thoracic traumatic complete spinal cord injury. They discovered higher PLMI in comparison with healthy controls. The probable explanation is the damage of descending pathways and loss of the supraspinal inhibitory influence (32, 33). It is also confirmed indirectly by the investigation of H-reflex recovery curve in PLMD patients. The results of this study demonstrated increasing late facilitation and decreasing late inhibition in comparison with controls (28). These findings might reflect decreased postsynaptic inhibition.

There is evidence that PLMS provokes a considerable increase in sympathetic activity throughout sleep (34, 35), which results in heart rate and blood pressure increase (9, 36). The repeated increase in nocturnal heart rate and blood pressure are considered to be the reason for the negative influence of PLMS on the cardiovascular system. Nevertheless, some researchers deny the existence of persistent sympathetic hyperactivity in the absence of movement (in other words, sympathetic hyperactivity exists only when PLMS occurs) (37, 38). On the other hand, other authors highlighted the primary role of the sympathetic nervous system in the generation of PLMS (39). Thus, there is no consensus on whether the PLMS itself can change the autonomic tone.

PLMS is often associated with EEG arousals. It is not yet established whether one phenomenon is the reason for the other, or both phenomena have the same origin. However, the latter seemed more likely (22, 40). The effect of arousals on daytime consequences is controversial. The high frequency of PLMS with arousals during sleep could be a hypothetical trigger for nocturnal arrhythmias and hypertension (41), and PLMS-related arousals may be a risk factor of ventricular arrhythmia (42). However, the majority of the researchers do not emphasize the difference between the PLMS with arousals and the PLMS without arousals. There are data showing that PLMS frequency (with and without arousals) is associated with a significant increase in systolic blood pressure (10, 43).

However, evidence of the relationship between PLMS and cSVD is scarce. The prevalence of PLMS in the cSVD subpopulation was not evaluated. Coelho et al. showed that patients with a history of stroke had a greater prevalence of PLMS and significantly higher mean PLMI than controls (44), but according to the research made by Manconi et al., PLMS are equally frequent in patients with a history of stroke or TIA and the general population (45). There are data about a higher prevalence of RLS in patients with cardiovascular diseases (7.7–36%), which is three times higher than the prevalence of RLS in the general population (46). The cardiovascular effects of RLS are suggested by some researchers to be mediated by increased PLMI (47).

Current evidence suggests that there is repetitive sympathetic activation accompanying PLMS during night sleep. This phenomenon could be a potential link between PLMS and negative impact on the cardiovascular system (36). The presumed cardiovascular effects of PLMS could underlie reported associations of higher PLMI with arterial hypertension severity (48), the incidence of cardiovascular events (49), increased risk of death in patients with systolic dysfunction following acute decompensated heart failure (50), and mortality risk in patients with systolic heart failure (12). It is reasonable to assume that PLMS-related activation of the sympathetic nervous system could be an explanation of the negative role of PLMS in CVD course, although it remains an underinvestigated issue. It is shown in cross-sectional studies that the severity of PLMS is associated with the extent of white matter hyperintensities (WMH) in patients with cSVD (51, 52) and in patients with first-ever minor stroke or transient ischemic attack (53). On the other hand, it is known that any pathological state accompanied by sleep fragmentation (sleep apnea, PLMS, and insomnia) may increase the risk of vascular diseases (9). Therefore, a more general process could be responsible for increased cardiovascular risk in PLMS patients.

Another unresolved question is the relevance of PLMS to cognitive dysfunction. Whereas, PLMS could worsen the course of cSVD, the greater cognitive decline of PLMS patients is expected. However, only a few studies focused on this issue, and their results suggest a positive correlation between the PLMI and cognitive decline. Significant association of higher PLMS frequency with impaired executive function was demonstrated among older men without dementia (54), patients with Parkinson's disease independent from psychomotor speed (55), and patients with cSVD (52). Besides, worse sleep efficiency has been also shown to be associated with poorer performance in tasks evaluating the executive domain (56), but the influence of PLMS on sleep quality and its ability to lead to sleep fragmentation is disputable. Moreover, some authors report that age-related changes in sleep architecture with a decline in slow-wave sleep might mediate age-related decline in executive control (57). It appeared confusing since the prevalence of PLMS increases with age too.

On the contrary, the cognitive impairment in cSVD is fully investigated, and it involves similar changes in executive functions, attention, language fluency, and set shifting (58, 59). MRI features of cSVD are summarized in STRIVE criteria (STandards for ReportIng Vascular changes on nEuroimaging). They consist of WMH, recent small subcortical infarcts, lacunes, cerebral microbleeds, and perivascular spaces (4). Substantial contribution to cognitive decline has been shown for frontal- and temporal-located cerebral microbleeds (60), progression of periventricular WMH (61), accumulation of lacunar infarctions (58), and perivascular spaces in combination with other markers (62).

### Rationale

The determination of the role of PLMS in the progression of cSVD MRI features and increase of cognitive dysfunction would create a new approach to patient management. Confirming of the negative impact of PLMS on the course of cSVD makes considerable further investigation the utility of the pharmacologic correction of PLMS in future studies. Currently, there is no generally accepted point of view on clinical significance of PLMS and its exact connection with both cSVD course and cognitive decline.

### Hypothesis

PLMI equal to or more than 15 movements per 1 h of sleep is a predictor of small vessel disease progression.

Null hypothesis: the presence of PLMS with index ≥ 15/h has no influence on cSVD course.

Alternative hypothesis (one sided): the presence of PLMS with index ≥ 15/h worsens cSVD course.

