### Statistical Analysis and Sample Size Calculation

The baseline values of MRI scale scores and cognitive tests (listed in Table 1) will be subtracted from the corresponding follow-up values, and percent change from baseline will be calculated. Based on the PLMI (≥15/h or <15/h), two groups will be formed. In order to reproduce results of the cross-sectional study conducted by Kang et al. (51), group comparisons will be made using the Mann–Whitney test for non-parametric statistics or unpaired *t*-test, depending on whether the distribution is normal. To assess the association between the PLMI and total cerebral SVD sum score, as well as WMH volume, Fazekas Scale score, and Scheltens Scale separately, Spearman correlation analysis will be applied. To confirm the data obtained by Leng et al. (54) and complement it with a more detailed cognitive assessment, logistic regression will be utilized to study the association between PLMS and clinically significant changes in cognition from the baseline to the follow-up visit.

Multiple regression analysis will be used to estimate the capability of each of the characteristics of PLMS (LMs, LMI, PLMI, PI, and SILMS index) to predict each of the outcome variables (except for stroke incidence and mortality rate). Adjustment for main predictors of cardiovascular risk (age, hypertension level, body mass index, diabetes mellitus, ischemic heart disease, cholesterol level, and smoking) will be made to determine if the associations are independent of these factors. Comparison of stroke incidence (separately for cerebral infarct, non-traumatic intracranial hemorrhage, and transient ischemic attack) as well as mortality rate due to stroke between two groups will be made using Pearson's chi-square test.

Spearman correlation test will be applied to evaluate the association between the PLMI and scores of self-reported questionnaires (listed in Table 1) and assess the influence of PLMS on sleep quality, mood, and daytime functioning. The level of statistical significance will be set at *p* < 0.05. All statistical analyses will be performed using SPSS version 21.0 (SPSS Inc., Chicago, IL, USA).

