Since the progression of cSVD features depending on PLMI is the key point of our study and linear regression will be applied, we calculated the sample size (N) based on this type of design. As mentioned above, there are seven independent variables (*p* = 7): age, arterial hypertension level, body mass index, blood sugar level, ischemic heart disease, cholesterol level, and smoking duration, and one tested parameter (PLMI or other parameters of PLMS). The sample size should be calculated depending on effect size: N = 392 + p for small, N = 52 + p for medium, and N = 22 + p for large effect size respectively (104). Thus, for revealing medium effect size, N = 52 + 7 = 59 participants should be enrolled, and for revealing small effect size, N = 392 + p, or 392 + 7 = 399 participants should be enrolled. A large effect size of PLMS is not expected. Therefore, 59 patients should be enrolled initially, and when no effect is revealed, the sample size should be enlarged up to 399. On the other hand, a comparison of cSVD feature prevalence between two groups is also planned as interim analysis. For this purpose, unpaired *t*-test (or Mann–Whitney test, depending on whether the distribution is normal) will be applied, and it requires standard deviation (SD) to calculate the sample size. When SD = 1.22 [obtained by Kang et al. (51)] and given probability for rejecting the null hypothesis α = 0.05, probability of failing to reject the null hypothesis under the alternative hypothesis β = 0.2 and effect size = 0.5, group size *N* = 49 is received when rounded up to the next highest integer. Therefore, at least 49^*^2 = 98 patients should be enrolled, but this number could be changed after another value of SD will be received.

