## Discussion

PLMS are regarded as the possible sign of repetitive autonomic dysfunction during night sleep. Nevertheless, it is not known if this autonomic dysfunction can worsen the course of cardiovascular pathology, as well as increase the risk of cardiovascular events. In this regard, the investigation of the long-term effects of PLMS seems to be worth researching.

The proposed protocol of the study allows estimate influence of PLMS on both the course of cSVD and incidence of stroke. WMH increase and cognitive decline, which are the key features of cSVD progression, will be assessed. In comparison with the researches conducted by Kang et al. (51) and Del Brutto et al. (105), our study has a longitudinal observational design, which seems to be more appropriate for the purpose of risk factors identification than a cross-sectional design. These researchers came to the opposite conclusions in their studies that seem to support the utility of further investigation of the problem. Besides, the proposed protocol suggests a more detailed MRI assessment. Estimation of different brain regions separately is another strength of our study.

In comparison with another prototype study conducted by Leng et al. (54), the proposed study has also some strengths. The neuropsychological examination is more detailed and comprehensive. Particular attention is paid to the assessment of executive functions since they are affected by vascular cognitive impairment to a greater extent.

The results of the proposed research have potential practical value because PLMS is a treatable condition. If PLMS is identified as a predictor for cSVD progression, it could be regarded as a modifiable risk factor for cSVD, which can be managed. Eventually, it may contribute to improving patient outcomes.

Several limitations of the study should be considered. The design of the study does not allow to reveal the exact mechanism of how PLMS leads to cSVD progression and cognitive decline. If the hypothesis of the research is confirmed, we will be able to assume the possible underlying process only. Finally, because of the short follow-up period, no differences between groups might be yielded and the role of PLMS can be underestimated.

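### The alternative is declared one-sided, p < 0.05 is given no side, and the regression sample size matches a two-sided test, so the threshold for claiming harm is unresolved

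*Protocol article*

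**What the plan says.** The Hypothesis section of the protocol article gives a formal pair. The null is "Null hypothesis: the presence of PLMS with index ≥ 15/h has no influence on cSVD course", and the other half is "Alternative hypothesis (one sided): the presence of PLMS with index ≥ 15/h worsens cSVD course". No alpha is attached there.

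The section Statistical Analysis and Sample Size Calculation says "The level of statistical significance will be set at" p < 0.05, with no side. Group comparisons use the t-test or the Mann–Whitney test, associations are estimated by multiple regression, and stroke events and stroke mortality are compared by Pearson's chi-square.

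The same section sizes the regression from a cited rule: "N = 392 + p for small, N = 52 + p for medium, and N = 22 + p for large effect size". With p = 7 this becomes "N = 52 + 7 = 59 participants should be enrolled" for a medium effect and "392 + 7 = 399 participants should be enrolled" for a small one. The plan starts with 59 and expands to 399 if the first stage shows no effect. A second calculation, for the group comparison, uses SD 1.22, α = 0.05, β = 0.2 and effect size 0.5, and arrives at 49 per group. It names no side either.

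**The concern.** Written next to a formal null, a one-sided label specifies a test; it does more than state an expectation. If p < 0.05 is read with that label, the plan tests for harm at one-sided 0.05. If it is read with the regression sizing, the plan tests at two-sided 0.05. The article does not say which.

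The two readings disagree for any harm-direction result with a two-sided p between 0.05 and 0.10. Such a result is a positive finding on one reading and a null finding on the other. Because enrolment beyond 59 depends on whether an effect is seen, the same result also decides whether 399 − 59 = 340 more patients are recruited. Left open, the choice could be made after the data are seen.

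**Working it through.** **Inputs.** From the article: constants 392, 52 and 22; p = 7; N = 59 and 399; α = 0.05; β = 0.2; SD = 1.22; effect size 0.5; 49 per group. Assumed, because the article does not give them for the regression rule: f² = 0.02, 0.15 and 0.35 for small, medium and large effects, and 80% power.

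**1. Reproducing the regression constants.** Constant = (z for alpha + z for power)² / f².

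- Two-sided 0.05: (1.9600 + 0.8416)² = 7.849.
- One-sided 0.05: (1.6449 + 0.8416)² = 6.183.

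| Effect | f² | Article | Two-sided 0.05 | One-sided 0.05 |
|---|---|---|---|---|
| Small | 0.02 | 392 | 392.4 | 309.1 |
| Medium | 0.15 | 52 | 52.3 | 41.2 |
| Large | 0.35 | 22 | 22.4 | 17.7 |

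All three printed constants match the two-sided column and none matches the one-sided column. One-sided sizing with p = 7 would give about 309 + 7 = 316 and 41 + 7 = 48, instead of 399 and 59.

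**2. Does the mismatch cost power?** Power for one regression coefficient from the noncentral t, with noncentrality √(f²N) and N − 8 degrees of freedom:

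| N | f² | Two-sided 0.05 | One-sided 0.05 |
|---|---|---|---|
| 59 | 0.15 | 0.8311 | 0.9015 |
| 399 | 0.02 | 0.8045 | 0.8800 |

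Both readings reach 80%, so there is no shortfall.

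**3. Thresholds.** The critical z is 1.960 for two-sided 0.05 and 1.645 for one-sided 0.05. Under the null, the chance of a false claim of harm at a single look is 2.5% or 5%.

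**4. Does the 49-per-group figure settle the side?**

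- Unpaired comparison, difference 0.5, SD 1.22: 2 × 7.849 × 1.22² / 0.5² = 93.5, so 94 per group two-sided; 2 × 6.183 × 1.22² / 0.5² = 73.6, so 74 one-sided.
- Unpaired comparison, 0.5 read as a standardised effect: 2 × 7.849 / 0.25 = 62.8, so 63 two-sided; 2 × 6.183 / 0.25 = 49.46, so 50 one-sided.
- One-sample or paired t-test, standardised effect 0.5/1.22, two-sided: 48.7, which rounds up to 49.

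One route close to 49 is one-sided. The only route that rounds up to exactly 49 is two-sided but is not the unpaired test the article names. The side cannot be read off.

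**The case against.** The strongest reply is that nothing printed is strictly contradictory. The article states no f², alpha or power for the regression rule, so its two-sidedness is inferred from assumed benchmarks. Two-sided sizing is also harmless to a one-sided test. A one-sided 0.05 test fixed in advance has a total type I error of 5%, which is the level the article names, and the authors give reasons for their direction: the Abstract expects a negative role, and the section on pathophysiology and cardiovascular effects cites cross-sectional associations with white matter hyperintensities. Finally, the side of individual tests is often left to an analysis plan.

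Much of this stands. The inference is not a statement by the authors, although a match on three constants out of three makes it strong. There is no loss of power. A one-sided 0.05 test could be defended if it were stated. The last argument does not remove the point, because the side was not left out: it was declared in the Hypothesis section and does not carry through to the significance level or the regression sizing.

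Two stronger readings are tempting and not supported. A reader might infer from "These researchers came to the opposite conclusions in their studies" in the Discussion that earlier evidence points both ways, so that a one-sided alternative is unjustified. The article does not say what the conclusions were; they may be association against no association. A reader might also take Pearson's chi-square, which rejects in either direction, as proof that the primary test is two-sided. It is applied only to stroke events and stroke mortality, which the Outcomes section lists as secondary. The t-test, Mann–Whitney test and regression can each be run with either side.

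**Conclusion.** The point holds as an inconsistency in the decision rule. The declared alternative is one-sided, the significance level has no side, and the regression sizing corresponds to two-sided 0.05 with 80% power, given f² = 0.02, 0.15 and 0.35. The threshold for claiming harm is therefore unresolved, and so is the rule that moves enrolment from 59 to 399. The 5% and 2.5% figures apply to one look only; they do not describe the error of the two-stage enrolment as a whole.

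A reader might infer that the study is too small for its hypothesis, or that every sample-size figure is two-sided. Neither follows: the regression sizes exceed what a one-sided test needs, and the 49-per-group figure has no identifiable side.

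**What to change.** State once, in the statistical section, that the primary and regression tests are two-sided at 0.05, and reword the alternative to match. If the directional alternative is kept, state one-sided 0.025. State that the same threshold decides whether an effect has been seen at 59 patients. Describe the chi-square comparisons of secondary events as non-directional.

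This costs about a sentence, and the regression figures 59 and 399 stay as they are. The group-comparison calculation needs more: name the formula, say whether 0.5 is a raw difference or a standardised effect, state the side, and recheck the 49 per group. For an unpaired two-sided test, the normal approximation gives 63 per group if 0.5 is standardised, or 94 if it is a raw difference with SD 1.22, so the total of 98 may change.
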